### 3.5. Study Staff

A team of exercise coordinators, under the supervision of the coordinating investigator of the study, will perform screening visits, supervise and organize the implementation of the study in the roll-out phase (between V0 and V1), supervise and participate in all study visits, and monitor adherence to the training and SOPs by the local exercise therapists.

The local exercise teams (three to five trainers per dialysis center) will receive special training ahead of the intervention by experts in exercise nephrology (ReNi e.V., Berlin, Germany: Society for Exercise in the Rehabilitation of CKD Patients) and conduct every training session at IG center site.

In addition, one documentation assistant (from the dialysis nursing staff) at each study site will be responsible for coordinating the study visits and for the documentation of all the study data (not related to the exercise intervention) and physical functioning assessments. 

### 3.6. Data Handling and Data Management

Data will be managed with REDCap™ Version 8.6.5, a fully web-based remote electronic case report form (eCRF; REDCap Consortium, [contact]). Data input into the primary eCRF database will be derived from several sources: 1. Direct input on the web-based eCRF, 2. Digitized survey data (questionnaires), 3. Uploaded training data from cycle ergometers and 4. Data extraction from the digital KfH-QiN dialysis registry via a custom interface. All patient data will be stored under a unique DiaTT identifier (DiaTT-ID) without other identifying information. 

The KfH-QiN patient registry is a digital registry database [17], which has been established before and independently of the DiaTT study for the quality improvement, analysis and scientific research of routine patient care data in all KfH dialysis centers. A specified dataset, which summarizes patient data collected between study visits, will be extracted from KfH-QiN and transferred into the DiaTT trial database. Data will be regularly reviewed for completeness, consistency and plausibility. There will be no on-site monitoring of data entry.

After the locking of the eCRF, the eCRF database will be merged with a claims dataset from participating health insurance companies, using the unique DiaTT-ID for matching.

This total DiaTT study database will be used for statistical analysis. Access to these data will be limited to the Clinical Trials Unit at Freiburg University for statistical analysis and to members of the steering board.

### 3.7. Statistical Planning and Analysis

Before the start of the final analysis, a detailed statistical analysis plan (SAP) will be prepared and completed during a “blind review” of the data before the database is locked. All statistical programming for analysis will be performed with the Statistical Analysis System (SAS Version 9.2, Cary, NC, USA).

#### 3.7.1. Sample Size Calculation

The sample size calculation is based on the primary objective of the trial, which is to demonstrate a difference between treatment groups after 12 months with respect to STS60. Assumptions are based on a single-arm trial in which the exercise training program was applied [9]. 

For STS60, mean ± standard deviation (SD) were reported: 16.7 ± 8.3 at baseline, 20.5 ± 8.8 after 6 months, 24.5 ± 10.2 after 12 months. Thus, a conservative assumption is 16.5 repetitions in the control group and 20.5 repetitions in the training group, i.e., a difference between treatment groups of 4 repetitions, and a standard deviation of 11.4. The corresponding standardized treatment effect (effect size) is then 4/11.4 = 0.35.

In order to detect a significant difference between the treatment groups at a two-sided level of α = 5% with a power of 80% under these assumptions, 130 patients per group (260 total) are necessary in an individually randomized trial. Cluster randomization must be considered in terms of a design factor. The average cluster size, m, is estimated as m = 50 patients. According to the CONSORT statement, small values (<0.05) are typical for the intraclass correlation coefficient (ICC). Thus, ICC = 0.05 represents a conservative assumption. The corresponding design factor is 1 + (m − 1) ICC = 3.45, and the required sample size is n = 897. Anticipating a mortality that is estimated to be <20%, at least 1100 patients will be randomized.

#### 3.7.2. Definition of Populations Included in the Analysis 

In the modified full analysis set (FAS), analyses of effectiveness will be performed according to the intention-to-treat (ITT) principle. All patients who have at least one post-baseline observation will be analysed in the treatment arms to which they were randomised, irrespective of whether they refused or discontinued the treatment or whether other protocol violations are revealed. A per-protocol (PP) analysis will be performed for sensitivity.

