## 2. Experimental Design and Methods

### 2.1. Study Design

DiaTT will be an interventional, cluster randomized (1:1), multicenter, controlled trial. After screening of dialysis centers and patient recruitment, 28 centers will be cluster randomized to IG or UC, as depicted in Figure 1. The randomization of centers will be stopped once a minimum of n = 1100 patients have been recruited. The intervention will consist of 12 months’ combined exercise training (aerobic and resistance), initiated after the baseline visit (V1), compared to UC without intervention.

The primary endpoint will be a change in the Sit-to-Stand (STS60) test result [15] from baseline to 12 months between groups. Secondary endpoints will include physical functioning (Timed-Up-and-Go test (TUG)), the Six-Minute Walk test (6MWT), the Grip Strength Test (GST)), frailty (Multidimensional Prognostic Index (MPI)), quality of life (SF-36), 3-point Major Adverse Cardiovascular Events (MACE), hospitalizations, overall survival, quality of HD (measured as serum phosphate and other laboratory values), medication (phosphate binders, erythropoietin), health literacy (HLS-EU-Q16 Health Literacy Questionnaire) and health economics (total costs of medication, hospitalization, therapeutic remedies, transportation, medical assistance tools, nursing care and sick leave from workplace). 

The study has been registered at ClinicalTrials.gov NCT03885102.

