### 3.2. Visit Schedule

Patients in eligible centers will be informed (in writing and orally) and screened for eligibility at V0. Two dedicated members of the study staff will conduct the screening visits in all centers to ensure the consistent communication of study-related information and recruitment. After written informed consent is obtained, centers will be randomized to either IG or UC, respectively. Patients will undergo baseline examinations (V1) three months after screening (V0), after a roll-out phase for the delivery of exercise equipment and the recruitment of local exercise therapists at intervention sites. Clinical assessments and tests of physical functioning will be performed at V1 and repeated at 3, 6, 9 and 12 months (Visits 2–5). For details about the assessments see Table 1. 

To ensure consistency, only a dedicated group of specifically trained exercise therapists will conduct the assessments of physical functioning.

The documentation assistants in the dialysis units will receive specific training by geriatricians to administer MPI. Routine care parameters, which are recorded continuously in the digital patient registry (KfH-QiN), will be summarized automatically for each study visit and transferred to the eCRF.

Data on health economics will be derived from the participating patients who are insured at one of the three collaborating German health insurance companies (Techniker Krankenkasse, BARMER or AOK PLUS). 

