#### 3.7.4. Secondary Endpoints for Effectiveness

The analysis of the secondary effectiveness endpoints will be performed with the same type of mixed regression model as described for the primary endpoint.

Overall survival (OS) is defined as the time from randomization until death from any cause, or as time from randomization until the patient was last alive (censored observations).

The OS rate will be estimated and described using the Kaplan-Meier method. Further analyses incorporating relevant prognostic factors will be conducted with Cox proportional hazards regression models.

Cause-specific survival will be defined as time from randomization until death from a specified cause (sudden death; 3-point MACE (a composite of cardiovascular death, non-fatal stroke, or non-fatal myocardial infarction)). Patients who are alive will be considered as censored observations and death from other causes will be considered as a competing event. The estimation of cumulative incidence rates will be applied in order to account for the presence of competing events. 

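### Survival is timed from randomisation but analysed in a set that requires a post-baseline observation, so deaths before baseline (and, on one reading, up to month 3) cannot count

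*Protocol article*

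**What the plan says.** Section 3.7.2 gives one rule for the effectiveness analyses: "In the modified full analysis set (FAS), analyses of effectiveness will be performed according to the intention-to-treat (ITT) principle". The entry condition follows: "All patients who have at least one post-baseline observation will be analysed in the treatment arms to which they were randomised". The word *observation* is not defined.

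Section 2.1 lists "3-point Major Adverse Cardiovascular Events (MACE), hospitalizations, overall survival" among the secondary endpoints. Section 3.7.4, which covers the secondary effectiveness endpoints, states: "Overall survival (OS) is defined as the time from randomization until death from any cause". It continues: "Cause-specific survival will be defined as time from randomization until death from a specified cause". The specified causes are sudden death and 3-point MACE. Kaplan-Meier, Cox and cumulative incidence methods are planned. The section names no other analysis set and does not exempt survival from the rule in Section 3.7.2.

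On timing, Section 3.2 says: "After written informed consent is obtained, centers will be randomized to either IG or UC, respectively". Table 1 marks randomisation in the Visit 0 column. V1 follows three months after V0 in Section 3.2, but Table 1 puts V0 at month −2. The first visit after baseline, V2, is at month 3.

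**The concern.** The survival clock starts at V0, but entry to the analysis depends on something that can only happen after V1. A patient who dies in between has been randomised and has died within the period being analysed, yet is not in the analysis. Every patient who is in it has, by definition, survived that interval. This is selection on survival (immortal time), and it conflicts with the intention-to-treat description.

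The abstract presents mortality as one of the outcomes for which this will be the largest randomised trial in nephrology. Survival curves that start at randomisation but omit the earliest deaths would overstate survival in both arms. Allocation is known before V1, and patients cannot be unaware of an exercise programme. Early refusal or a missed first assessment could therefore also differ between arms.

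**Working it through.** **The plan's own figures.** Section 3.7.1 uses a standardised effect of 4/11.4 = 0.35, two-sided α of 5% and 80% power. The normal approximation gives 2 × (1.960 + 0.842)² / 0.35² ≈ 128.1, so 129 per group. The t-test solution is 129.1, so 130 per group, or 260 in total. The design factor is 1 + 49 × 0.05 = 3.45, and 260 × 3.45 = 897. Then 897/1100 = 81.5%, a loss of 18.5%, which fits a mortality below 20%. The chain reproduces and does not depend on this point. It supplies two inputs: 1100 patients and mortality below 20%.

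**Inputs**
- Randomisation to V1: r = 2 months (Table 1) or 3 months (Section 3.2).
- V1 to V2: 3 months. V1 to the end of follow-up: 12 months.
- 12-month mortality q: the plan gives only an upper bound without a time unit, so 10%, 15% and 20% are assumed.
- Also assumed: a constant hazard, equal mortality in both arms, 1100 patients at risk from randomisation at V0, and no other reason for missing V2.

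**Formulas.** The monthly hazard is h = −ln(1 − q)/12. The expected deaths before the set can be entered are 1100 × [1 − exp(−hL)]. On the lenient reading, where a recorded death after V1 counts as an observation, L = r. On the strict reading, where an observation is a visit assessment, L = r + 3.

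Example with q = 20%: h = 0.2231/12 = 0.01860. For L = 6, 1 − exp(−0.1116) = 0.1056, and 1100 × 0.1056 = 116.

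| q | Deaths before V1 (L = 2 to 3) | Deaths before V2 (L = 5 to 6) | Month-12 mortality, all randomised | Same, lenient set | Same, strict set |
|---|---|---|---|---|---|
| 10% | 19–29 | 47–56 | 11.6–12.3% | 10.0% | 7.6% |
| 15% | 29–44 | 72–86 | 17.3–18.4% | 15.0% | 11.5% |
| 20% | 40–60 | 98–116 | 22.9–24.3% | 20.0% | 15.4% |

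Mortality in all randomised patients is 1 − exp[−h(r + 12)]. In the lenient set only 12 months remain in which a death can count. In the strict set only 9 remain, so at q = 20% it is 1 − exp(−0.01860 × 9) = 15.4%.

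As a share of all deaths from randomisation to month 12, the excluded deaths are about 15–22% on the lenient reading and 37–43% on the strict one. The guaranteed survival time is 2 to 3 months or 5 to 6 months respectively. The ±2 week visit window widens the latter to 4.5 to 6.5 months.

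**The case against.** The strongest objection is to the strict reading. Section 3.7.2 says observation, not visit. Section 3.7.4 itself uses the word for censored survival times, Section 3.4 records deaths and hospitalisations without tying them to a visit, and registry data accrue continuously. A patient who dies in month 2 after V1 could well qualify. This stands: the 72–116 deaths and the 5 to 6 months depend on a reading that the document does not settle. It does not rescue the period before V1, because a death before baseline cannot be a post-baseline observation.

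Section 3.7.4 also names no set for survival, and an analysis plan that is not shown may do so. However, the general wording of Section 3.7.2 covers effectiveness analyses and survival is classed as one. The set and the time origin are both fixed in the article, and they do not fit together.

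Third, the V0–V1 interval is the same in both arms and training starts only after V1, so training cannot cause those deaths. With equal selection and proportional hazards, the Cox hazard ratio need not be biased. This also stands, and it limits the damage on the lenient reading mainly to the level of the curves.

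A reader might infer three stronger things that the document does not support:
- *That early deaths are missing from the safety analysis.* Section 3.7.2 restricts effectiveness analyses only, and Section 4.3 describes the safety comparison of hospitalisations and deaths without that condition.
- *That included patients are event-free early on.* They must be alive, but a patient with a non-fatal infarction or an admission who is later observed stays in, with the event. Only time to death carries guaranteed time. MACE loses its early fatal events and early competing deaths.
- *That the primary analysis is compromised.* The STS60 model needs a post-baseline value in any case.

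**Conclusion.** The point holds for the time-to-event secondary endpoints. On any reading, deaths between randomisation and V1 are excluded while the survival clock runs. This removes about 29–60 deaths at 15–20% mortality and guarantees 2 to 3 months of survival. If an observation means a visit assessment, the figures are 72–116 deaths (47–56 at 10% mortality) and 5 to 6 months.

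Kaplan-Meier and cumulative incidence estimates from randomisation are biased, survival is overstated, and the intention-to-treat label does not fit. The hazard ratio is at risk only if early death or early loss differs by arm, or if the effect changes over time. The document makes differential loss plausible but gives no evidence of it.

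The counts rest on reading the bound of 20% as 12-month mortality, on a constant hazard and on randomisation at V0. If a centre is randomised some time after a patient's V0, the gap for that patient is shorter. The finding itself needs only the order of randomisation, V1 and V2. It should be fixed before database lock, but it does not threaten the primary result.

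**What to change.** Keep the modified full analysis set for STS60 and the other repeated functional measures. For overall survival, cause-specific survival, 3-point MACE and hospitalisation, choose one of the following and state it:

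1. Analyse all consented patients of randomised centres, by randomised arm, from randomisation and with no post-baseline requirement. Confirm vital status for the V0–V1 interval.
2. Start the clock at V1 in all patients alive and enrolled at V1, and report deaths and other losses between V0 and V1 by arm.

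In either case, define *observation* wherever the modified set is kept, and reconcile the V0–V1 interval between Section 3.2 and Table 1.

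The cost is small. Section 3.7 has the analysis plan completed before database lock, so the wording can be settled there. Section 3.4 already has date and cause of death recorded on the eCRF. The SAE/AE row of Table 1 is not marked at Visit 0, so one vital-status item for the roll-out period may have to be added. Neither the design nor the sample size changes.

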#### 3.7.3. Primary Endpoint 

The primary effectiveness analysis will be performed in the modified FAS. A linear mixed-effects regression model will be applied for the primary endpoint, STS60, at different time points, including randomized treatment, baseline STS60, the stratification factor region, time points, and a time*treatment interaction. Clusters will be included as a random effect, and repeated measurements of patients will be accounted for with an exchangeable correlation structure. The time*treatment interaction terms will enable the estimation of the therapy’s effect at different time points. The treatment effect estimates will be presented with two-sided 95% confidence intervals.

The primary analysis will be adjusted for baseline STS60 measurements, as proposed in the EMA ‘Guideline on adjustment for baseline covariates in clinical trials’ (EMA/CHMP/295050/2013, Section 5.6). 

A mixed model enables the incorporation of patients with partly incomplete observations. However, missingness at random (MAR) may be questionable. Sensitivity analyses will be performed with multiple imputation methods investigating the structure and impact of missing values.

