However, contrary to this skepticism, in our experience of routine practice as well as our pilot study (46 HDpatients, age 63.2 ± 16.3 years, observation period up to 5 years), a supervised intradialytic exercise program, combining resistance and aerobic training twice weekly for 60 min, significantly improved exercise capacity, strength, quality of life and physical functioning and was associated with a high adherence rate of 78% after 1 year and 43% after 5 years, without safety issues [9]. Exercise was conducted by exercise therapists and did not require the involvement of the regular dialysis staff; it allowed the participation of patients with almost all clinical conditions or levels of disability and was found to integrate well with care processes in the dialysis unit.

The same concept will be applied in the current DiaTT trial, in which we will extend this experience from a single center to a multi-center context and substantially expand patient numbers, applying as few medical restrictions on participation as possible. By including only patients from one non-profit dialysis provider, the established dialysis structure, clinical assessment, clinical chemistry and data handling will be identical for all sites. The primary objective will be to assess the effectiveness of exercise training during HD compared to usual care (UC; no intervention) after 12 months. The intervention will combine strength and aerobic exercise training and add health literacy counselling (HLC). We will investigate clinical outcomes, such as frailty, morbidity, mortality and health economics, in order to facilitate the future implementation of intradialytic exercise into routine health care reimbursement, a request that has been made repeatedly by the nephrological community [6,10,11,12]. 

By including >1100 well-documented CKD patients in this large randomized study, the DiaTT trial, after completion, will be one of the three largest randomized, controlled trials comparing exercise intervention with the usual care in medicine, together with the HF ACTION trial, which included 2331 chronic heart failure patients over 30 months [13] and the Look AHEAD trial, which included 5145 obese patients with type 2 diabetes over 9.6 years [14]. 

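### The primary model names an exchangeable patient structure and one centre effect for a test read at month 12; the usual form of that model could make the test mildly liberal

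*Protocol article*

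**What the plan says.** Section 3.7.3 of the protocol article specifies a linear mixed model for STS60 over the post-baseline visits, "including randomized treatment, baseline STS60, the stratification factor region, time points, and a time*treatment interaction". The covariance is then stated: "Clusters will be included as a random effect, and repeated measurements of patients will be accounted for with an exchangeable correlation structure". Visit-specific effects come from the interaction: "The time*treatment interaction terms will enable the estimation of the therapy’s effect at different time points".

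The confirmatory question is at one visit. Section 2.1 defines the primary endpoint as the change from baseline to 12 months, and section 3.7.1 gives the aim as "to demonstrate a difference between treatment groups after 12 months with respect to STS60". Section 3.7.1 also gives the only STS60 SDs in the article, from the pilot: "16.7 ± 8.3 at baseline, 20.5 ± 8.8 after 6 months, 24.5 ± 10.2 after 12 months".

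The supporting analyses named are a per-protocol analysis (section 3.7.2) and multiple imputation (section 3.7.3). Neither varies the covariance structure.

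**The concern.** A model with one variance and one correlation for all visits pools its information about spread. The standard error at month 12 then reflects the average spread over months 3, 6, 9 and 12. If the spread around the baseline-adjusted mean is largest at month 12, that standard error is too small, the 95% confidence interval is too narrow, and the 5% test rejects too often.

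This can arise in two ways at patient level. The SD itself may grow, as it did in the pilot. Or the correlation with baseline may fade over the year, so that baseline adjustment removes less variance at month 12 than at month 3.

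At centre level, a single centre effect assumes that each centre deviates by the same amount at every visit. If centres shift between visits, the model treats the shift as patient-level noise and divides it by the number of patients, although only 28 centres carry that information.

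With missing visits the point estimate also leans on the covariance, because the model uses it to carry information from observed to unobserved visits.

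**Working it through.** **The plan's own figure.** With a difference of 4 and SD 11.4, n per group = 2 × (1.96 + 0.8416)² × (11.4/4)² = 127.5, so 128. The rounded effect size 0.35 gives 129, and the t-based calculation gives up to 130, as stated. The design factor is 1 + 49 × 0.05 = 3.45, and 260 × 3.45 = 897. The sample size reproduces and is not at issue.

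**Inputs from the article.** 28 centres (2.1); four post-baseline visits (3.2); ICC 0.05, 897 analysable patients and the pilot SDs (3.7.1). Patients per centre: m = 897/28 = 32.

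**Assumptions.** Complete, balanced data; SDs at months 3 and 9 interpolated as 8.55 and 9.5; one common variance fitted.

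**Formula.** Let c be the centre covariance and p the patient covariance over the four visits. For the month-12 mean of a centre:

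- true variance = c₁₂ + p₁₂/m
- variance reported by the model = (mean of all entries of c) + 3 × (mean diagonal of c − mean off-diagonal of c)/(4m) + (mean diagonal of p)/m

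The factor that turns this into a treatment contrast cancels. With R = √(reported/true), the size of the nominal 5% test is 2Φ(−1.96R). The patient correlations drop out: with complete data and constant variance, R = 1.00 and size is 5.0% whatever the true within-patient correlation. The harm comes from unequal variances, not from the correlation pattern alone.

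**1. Pilot-type SD growth.** Visit variances are 73.10, 77.44, 90.25 and 104.04, with mean 86.21.

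- Centre SD grows with patient SD: reported = 0.05 × 9.2625² + 0.95 × 86.21/32 = 4.290 + 2.559 = 6.850 (the middle term adds less than 0.001). True = 104.04 × (0.05 + 0.95/32) = 8.291. R = 0.909, size 7.5%.
- Centre SD constant: reported = 4.31 + 81.90/32 = 6.870. True = 4.31 + 99.73/32 = 7.427. R = 0.962, size 5.9%.

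**2. Fading baseline correlation, constant SD (assumed).** SD 9.3; correlation with baseline 0.85, 0.80, 0.75, 0.70. The model has one baseline slope, so the residual variance is 9.3² × [(1 − r²) + (r − 0.775)²]. Residual SDs are 4.95, 5.58, 6.16 and 6.68.

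- Centre SD grows with residual SD: reported 2.732, true 3.554, R = 0.877, size 8.6%.
- Centre SD constant at 5% of 9.3²: reported 5.404, true 5.718, R = 0.972, size 5.7%.

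**3. Both.** With the pilot SDs and the same fading correlations, residual SDs are 4.51, 5.28, 6.28 and 7.28.

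- Centre SD grows: reported 2.751, true 4.228, R = 0.807, size 11.4%. With correlations falling from 0.90 to 0.75 instead, R = 0.778 and size is 12.7%.
- Centre SD constant: R = 0.952, size 6.2% in either case.

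**4. Centre-by-visit correlation ρ below 1 (assumed), constant variance.** In units of the total variance, reported = 0.05 × [(1 + 3ρ)/4 + 3(1 − ρ)/128] + 0.95/32 and true = 0.05 + 0.95/32 = 0.0797.

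| ρ | reported | R | size |
|---|---|---|---|
| 0.9 | 0.0761 | 0.977 | 5.5% |
| 0.8 | 0.0724 | 0.953 | 6.2% |
| 0.5 | 0.0615 | 0.879 | 8.5% |

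**Simulation check.** Over 8,000 trials per scenario, tested against t with 26 degrees of freedom, size was 4.9% when the stated structure was true and 7.4% with pilot SDs and growing centre SD (empirical standard error 1.09 against 0.99 reported). A separate simulation with 5% loss per visit (28 centres of 39 patients, 4,000 trials per scenario) gave 4.4% when the structure was true, 5.9% to 8.3% with pilot SDs, 8.7% with fading correlation alone, and 11.4% to 12.7% with both.

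**The case against.** A reader might infer that the pilot SDs contradict the model and that the 5% test is certainly liberal. The article does not support that.

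- **Wording.** The text fixes an exchangeable correlation. It does not state a constant variance, and a version with visit-specific variances is compatible with it. An article may leave that detail to the analysis plan.
- **Population.** Everyone in the pilot trained. The SD rose while the mean rose from 16.7 to 24.5, and the coefficient of variation fell from 8.3/16.7 = 0.50 to 10.2/24.5 = 0.42. Spread that grows with a treatment-driven mean need not appear when there is no treatment effect, which is where type I error is defined.
- **Precision.** The pilot is described as "46 HDpatients, age 63.2 ± 16.3 years, observation period up to 5 years". Assuming about 36 of the 46 were measured at month 12 (78% adherence), (10.2/8.3)² = 1.51 gives p of about 0.19 if visits are treated as independent. A paired test gives 0.17 to 0.009, depending on an assumed correlation of 0.5 to 0.9.
- **Centres.** The pilot cannot speak to centre-by-visit variation. The article itself says "we will extend this experience from a single center to a multi-center context".
- **Size.** A type I error near 14% or 15% can be produced, but only by adding steeper correlation decay or unstable centre effects that no figure in the article supplies.

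All of this stands, and it limits the claim to a risk. It does not remove the point. Exchangeable usually means compound symmetry, and if another form is intended, the text should say so. Nor does the population argument cover everything, because fading correlation with baseline needs no SD growth and no treatment effect. The covariance is also a stated choice for the confirmatory test, so this is not a complaint about silence.

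**Conclusion.** The concern holds as a risk of modest size. For a month-12 test the article names a restrictive structure that, in its usual form, assigns month 12 an averaged variance, and no listed sensitivity analysis would reveal the problem.

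- If pilot-type SD growth occurs, the standard error is about 4% to 9% too small and the test runs at about 6% to 7.5%.
- If only the baseline correlation fades (assumed 0.85 to 0.70), size is about 6% to 8.5%.
- If both occur, size is about 11% to 13% when centre spread grows with residual spread, and 6.2% in the complete-data calculation when it stays constant.
- If only centre effects shift between visits (assumed correlation 0.9 to 0.5), size is about 5.5% to 8.5%.

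Only the pilot SDs are in the article. The correlations with baseline, the centre-by-visit correlation and the behaviour of the centre SD are assumptions. If variances are constant and centre effects stable, the stated model is sound. This should be fixed; confidence is moderate.

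**What to change.** In section 3.7.3, and in the analysis plan that is still to be completed before database lock (section 3.7):

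- Replace the exchangeable structure with an unstructured 4 × 4 within-patient covariance over months 3, 6, 9 and 12, which gives each visit its own variance.
- Add a centre-by-visit random effect to the centre effect.
- Use small-sample degrees of freedom suited to 28 centres.
- Pre-specify the fallback for non-convergence: a month-12 analysis of covariance with a random centre effect.

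The cost is wording only. The patient covariance has 10 parameters instead of 2, which at least 1100 patients support easily, and the centre-by-visit effect adds to that slightly. The confidence interval may be slightly wider. The 897 and 1100 do not change. Section 3.7.4 uses the same type of model for the secondary effectiveness endpoints, so the revised wording should carry over to those measured repeatedly.
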